#### Significance of the proposed study

This study fits within the first priority – Advancing Evidence Based Practice – of the EMDR Foundation. This study will increase the availability of quality EMDR research in the field of PD. Although the efficacy of EMDR was explored in a number of studies, more evidence is needed to implement EMDR in the treatment of patients with PD. Furthermore, this study might result in the addition of EMDR to the guidelines for treatment of (some types of) PD. Therefore, the study has the potential to arrange a breakthrough in the treatment of patients with PD worldwide.

#### *Value for clinical practice*

PD are prevalent and ensuing distress is high for the patients as well as their surroundings. Evidence suggests that patients with PD might be even more stigmatized than other psychiatric diagnoses, with both fear and frustration among the common public reactions to personality disorders (Sheehan, Niewegłowski & Corrigan, 2016). The belief that people with personality disorders should be able to exhibit control over their behavior results in symptoms being viewed as manipulations or rejections of help. However, almost all of these patients are traumatized, suffer from bad memories, severe mood swings, suspiciousness and difficulties to attach to others.

Treatment of PD has a long duration and is expensive. The number of therapists is insufficient. As a result, many patients are waiting for treatment. Furthermore, approximately half of these patients do not benefit from these interventions with the risk that patients drop out from treatment.

Another concern is that symptoms of trauma and PTSD can be easily missed or delayed at a department for PD. Caregivers might be used to focus on the symptoms of PD and patients might be ashamed to talk about their traumatic experiences. In clinical practice interventions for trauma are often just considered if treatment for PD stagnates. By conducting this study, we also aim to improve the attention for and recognition of symptoms of trauma and PTSD in patients.

EMDR therapy can be applied within a short period, i.e., a couple of weeks. it has proven to be safe and is the most cost-effective trauma-focused treatment (Mavranouzouli et al., 2020).

In addition, the literature suggests that EMDR not only decreases the severity of symptoms of trauma, but also symptoms of PD. If these findings can be confirmed in this RCT, EMDR might result in a decline of the duration of treatment of PD, the number of dropouts, waiting lists and societal costs.

#### *Scientific value*

Members of the project group are internationally considered as experts in the field of EMDR, PD, and cost-effectiveness studies. Although EMDR is the treatment of choice for PTSD, the literature regarding EMDR for PTSD among patients with PD is limited (Slotema et al., 2019; de Jongh et al., 2020). The same holds true for the efficacy of EMDR on the severity of symptoms of PD, presence of PD (de Jongh et al., 2020; Hafkemeijer et al., submitted) as well as interpersonal functioning. Cost-effectiveness studies are lacking. A RCT exploring differences between EMDR therapy and waiting list for the severity and presence of PD, trauma and cost-effectiveness is therefore urgently needed.

In addition, all RCTs investigating psychotherapy for PTSD are conducted with patients with BPD. Among open label studies only a minority of studies included patients with other PD. In clinical practice, patients with BPD comprise approximately 30% of the caseloads. It is of importance to pay more attention to other PD. By including patients with all types of PD, this study adds to the knowledge of treatment of other PD as well.

Finally, researchers in the field of other psychiatric disorders than PD might profit from this study as trauma is prevalent among other psychiatric disorders as well.

In order to inform other researchers about the procedure and results of this study, this study will be registered at [www.clinicaltrial.gov](http://www.clinicaltrial.gov).

## 2. OBJECTIVES

### *Primary Objectives:*

- 1) How effective is EMDR therapy compared to waiting list on symptoms of PD?
- 2) How cost-effective is EMDR therapy versus a wait-list control condition?

### *Secondary Objectives:*

- 3) What is the decline in the proportion of patients fulfilling a diagnosis of PD after EMDR?
- 4) How effective is EMDR therapy compared to waiting list on the severity of symptoms of PTSD?
- 5) How effective is EMDR therapy on mental health outcome, severity of difficulties in emotion regulation and interpersonal functioning?
- 6) What is the effectiveness of EMDR on quality of life?

### **3. STUDY DESIGN**

To assess the surplus value of EMDR compared to waiting list, a single-blind RCT with two groups (EMDR versus waiting list) will be performed. The experimental group will receive ten bi-weekly EMDR sessions of ninety minutes each (with a total duration of 5 weeks). Data will be collected at baseline, 5 weeks (post EMDR-treatment) and three-, six- and twelve-months after onset of the study.

Based on a feasibility analysis, inclusion of patients will take 1 year.

The study will be conducted at Parnassia Psychiatric Institute and GGZ Delfland.

## 4. STUDY POPULATION

### 4.1 Population

Participants will be recruited from outpatient clinics of the Parnassia Psychiatric Institute and GGZ Delfland. We aim to include a broad range of patients with PD, because this represents the population that is treated within outpatient, specialized mental health care centers for PD the best.

### 4.2 Inclusion criteria

In order to be eligible to participate in this study, a subject must meet all of the following criteria:

1. Age eighteen years or older
2. PD classified with the aid of the Structured Clinical Interview for DSM-5 for PD
3. Distress due to traumatic experiences

### 4.3 Exclusion criteria

A potential subject who meets any of the following criteria will be excluded from participation in this study:

1. Estimated IQ below seventy
2. Inadequate competence in the Dutch language

### 4.4 Sample size calculation

In order to test the effectiveness of EMDR in reducing the number of PD symptoms over time, relative to waiting list, a linear mixed model (LMM) with intention-to-treat will be used. The RCT of five EMDR sessions revealed an effect size of 0.65 for change in psychological symptoms (Brief Symptom Inventory), 0.62 for psychological functioning (Outcome Questionnaire-45) and 0.56 for change in personality functioning (General Assessment of Personality Disorder) (Hafkemeijer et al., 2020). Since change in personality functioning is also (primarily) assessed in the current study, although with the aid of a different measure (ADP-IV), the effect size for the main analysis is expected to approximate the effect size found by Hafkemeijer et al., 2020. With the aid of standardization by post score standard deviations (standard procedure for meta-analyses) this effect size decreases to 0.46. Therefore, an effect size of 0.43 was estimated to be appropriate for this study. Using Liu and Liang's (1997) equation, assuming a correlation of 0.7 between five repeated measurements, a treatment effect size of 0.43, a power of 0.8, an  $\alpha$  significance level of .05, and two treatment conditions, the power analysis

resulted in a total sample size of 132 persons. With an estimated dropout rate of 20% a total of 159 patients is needed. With participation of 6 departments within two institutions our estimation is that it is feasible to include this number of patients within one year.

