## 8.3 Study procedures

1. Patients will be recruited in two ways; 1. by means of posters hanging in the waiting room; patients can announce themselves to their treating therapist/physician or contact the researchers directly 2. Patients with a PD will be informed by the therapist/physician about the study. The therapist/physician informs the researchers, who will send information to the patient by mail and call the patients to invite them for an appointment. Interested patients will receive further information about the study during an appointment with one of the researchers. Furthermore, the researcher will check eligibility for inclusion. At the end of the appointment patients will be given informed consent forms. The patients are allowed to take the time they need to make a decision about participation. Patients who decide to participate will be asked to sign informed consent.
2. Diagnostic instruments before inclusion: a. Any PD diagnosis will be confirmed using the SCID-5-PD
3. Informed consent: During an intake interview with the researchers, patients are informed about the study verbally and formally. If the patient had enough time to consider whether he/she wants to participate into this study, the patient is asked to give written, informed consent.
4. Randomization: After patients are included and have given informed consent, patients are randomized into one of the two conditions.
5. Questionnaires will be administered at baseline (before randomization), after weeks (post EMDR) and three, six and twelve months after onset of the study.
6. Interview: all participants in the EMDR group will be requested to participate in a qualitative interview about their experiences with EMDR therapy.
7. Patients in the experimental group are treated with ten biweekly, ninety minute, EMDR sessions. These patients are compared with a waiting list condition. After three months of follow-up patients can decide whether they want to have standard treatment for PD.

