### 10.1 Primary study parameter(s)

The primary study parameter is the number of diagnosed PD symptoms, over five moments of measurement. In order to test the effectiveness of EMDR in reducing the number of PD symptoms over time, a linear mixed model (LMM) with intention-to-treat will be used. Within-subjects factor 'Time' has five levels (baseline vs. post-intervention vs. three-month vs. six-month vs. twelve-month follow-ups) and between-subjects factor 'Group' has two (EMDR vs. waiting list). Corrected post-hoc analyses will be performed where significant effects are found.

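### The 80% power in section 4.4 is for a five-measurement average that counts the pre-randomisation baseline, so it belongs to neither group test in the section 10.1 model

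*Protocol*

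**What the plan says.** Protocol section 4.4 plans a linear mixed model on the number of PD symptoms and takes the sample size from a repeated-measures formula: "Using Liu and Liang's (1997) equation", with "assuming a correlation of 0.7 between five repeated measurements, a treatment effect size of 0.43, a power of 0.8". One effect size is used: "an effect size of 0.43 was estimated to be appropriate for this study". The calculation "resulted in a total sample size of 132 persons" before the allowance for dropout, which raises the number to 159.

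Section 10.1 identifies the five measurements as baseline, post-intervention, and 3, 6 and 12 months. All five are levels of the within-subject factor Time, and the "between-subjects factor 'Group' has two (EMDR vs. waiting list"). The section does not say whether the Group main effect, the Time by Group interaction or a contrast at one visit is the confirmatory test.

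Section 8.3, item 5, fixes when the first measurement is taken: "Questionnaires will be administered at baseline (before randomization").

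**The concern.** The formula, used with one effect size and five measurements, describes a group difference of the same size at every measurement. Randomisation makes the expected difference at baseline zero, so one of the five measurements is credited with an effect that it cannot show.

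Nor does the figure describe the interaction. That term asks whether the group difference changes across visits, and a constant difference at all five measurements would leave nothing for it to detect. The 80% therefore cannot be carried over to either group term of the planned model. Because 10.1 leaves the term open, a reader cannot tell whether the real power is well below or well above the stated value.

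**Working it through.** **Inputs.** From 4.4: d = 0.43 (SD = 1), ρ = 0.7, m = 5, α = 0.05, power 0.80, N = 132. From 10.1 and 8.3: the first of the five measurements precedes randomisation. Assumed here: equal allocation (66 per arm), the same correlation between every pair of visits, and a two-sided test. A one-sided test would give 102 to 104 patients, not 132.

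**Step 1: reproduce 132.** For a time-averaged difference, N = 4(1.960 + 0.842)² × V / d², with V = [1 + (m − 1)ρ]/m.
- m = 5: V = 3.8/5 = 0.76 and N = 4 × 7.849 × 0.76 / 0.1849 = 129.0, or 130 in equal arms. With the t distribution, 80.0% is reached at 131, and 132 gives 80.3%.
- m = 4 (post-baseline visits only): V = 3.1/4 = 0.775 and N = 131.6, so 132.

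The stated figure reproduces. It does not by itself show which version was run, but 4.4 says five measurements.

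**Step 2: Group main effect with zero difference at baseline.** Let the difference be 0.43 at all four later visits. The five-level mean is 4 × 0.43/5 = 0.344. The expected test statistic is 0.344/√(2 × 0.76/66) = 2.267, and power is 62.1% (normal) or 61.4% (t). For 80%, N = 4 × 7.849 × 0.76/0.344² = 201.6, so 202, or 204 with the t distribution.

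**Step 3: Time by Group interaction, 4 df.** The differences (0, 0.43, 0.43, 0.43, 0.43) have sum of squares about their mean 0.344² + 4 × 0.086² = 0.1479. The non-centrality is (66/2) × 0.1479/(1 − 0.7) = 16.27, and power is 91.7% (chi-square) or 91.4% (F).

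**Step 4: one visit, adjusted for baseline.** The residual variance is 1 − ρ² = 0.51. The expected statistic is 0.43/√(2 × 0.51/66) = 3.459, and power is 93.0% (t). With 159 × 0.8 = 127 analysed it is 92.0%.

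**Step 5: dependence on ρ** (0.43 at all later visits; t-based except the interaction, which uses chi-square).

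| ρ | Group main effect, N = 132 | Time by Group, N = 132 | One visit, baseline-adjusted, N = 132 | Same, N = 127 |
|---|---|---|---|---|
| 0.5 | 72% | 70% | 81% | 79% |
| 0.6 | 66% | 81% | 87% | 85% |
| 0.7 | 61% | 92% | 93% | 92% |
| 0.8 | 57% | 99% | 98% | 98% |

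**Step 6: a waning difference.** Section 5.1 offers controls standard treatment after three months, so a constant difference to 12 months is not assured. If the difference halves at 6 and 12 months (an assumption made here), the five-level mean is (0.43 + 0.43 + 0.215 + 0.215)/5 = 0.258. At ρ = 0.7 the main effect then has about 40% power and the interaction about 87%.

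**The case against.** - **A reader might infer that the trial is underpowered.** The documents do not support that. Power at ρ = 0.7 is below 80% only if the Group main effect over all five levels is the test, and the protocol does not say it is. Section 4.4 states its aim as a reduction over follow-up compared with the waiting list, its effect size is derived from change scores, and 10.1 has both factors. The more natural reading is the interaction or a change from baseline. On the protocol's own inputs these have about 92% and, for change at one visit, 89%. This part of the objection stands.
- **A reader might infer an arithmetic error.** There is none, since 130 to 132 follows from the stated inputs. An average over the four post-baseline visits also needs about 132 (80.1% by the normal formula), so dropping baseline from the count barely changes the number. But 4.4 counts five measurements, and 10.1 does not name that four-visit average as the test.
- **Baseline as a level of Time is an accepted analysis.** True. Baseline adjustment is more efficient (93% against 89% for one visit at ρ = 0.7), but the unadjusted form is not an error.
- **The tested term may be fixed in a statistical analysis plan.** It may, and its absence from 10.1 is not the point by itself. The mismatch remains because the power claim and the five-level model both stand in the protocol.
- **A reader might infer that the interaction is safely overpowered.** That holds only near the assumed correlation: at ρ = 0.5 it has about 70%.

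**Conclusion.** The point holds as a mismatch between the sample-size calculation and the planned test. The 80% applies to a difference of 0.43 at all five measurements, which the design rules out at baseline. In the model of 10.1 it fits neither the Group main effect (about 61%) nor the 4-df Time by Group test (about 91% to 92%). These figures rest on N = 132, ρ = 0.7 between all pairs of visits, equal arms, a two-sided 5% test and a sustained difference of 0.43 after baseline. Across ρ from 0.5 to 0.8 the main effect runs from 72% down to 57% and the interaction from 70% up to 99%. Whether the trial has enough power depends on the term chosen and on the true correlation. The documents do not settle either, so neither a shortage nor a surplus of power can be asserted.

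**What to change.** In 10.1, take the post-baseline visits as the outcome, with baseline ADP-IV as a covariate or with baseline means constrained equal across arms. Name one primary contrast. The group difference at 3 months is a natural candidate because it precedes the offer of standard treatment to controls.

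In 4.4, replace the five-measurement calculation by the power of that contrast at d = 0.43: about 93% with 132 analysed and 92% with 127 at ρ = 0.7, and about 81% and 79% at ρ = 0.5. Give the range, not only the value at 0.7.

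The cost is a rewording of two sections and one recalculation, to be done before any outcome data are analysed. No patients are added. The drawback is having to disclose that power is marginal if the correlation is near 0.5.

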##### **8.4.1 Specific criteria for withdrawal (if applicable)**

#### **8.5 Replacement of individual subjects after withdrawal**

Inclusion is continued until 159 participants have been included. We attempt to collect reasons for withdrawal. However, patients are not obliged to give a reason.

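### The 20% dropout allowance is computed as 132 × 1.2 = 159 instead of 132 / 0.80 = 165: a minor arithmetic correction to section 4.4

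*Protocol*

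**What the plan says.** Protocol section 4.4 gives the inputs of the power analysis: "assuming a correlation of 0.7 between five repeated measurements", "a treatment effect size of 0.43, a power of 0.8", and a "significance level of .05, and two treatment conditions, the power analysis". It names the Liu-Liang equation and reports that this "resulted in a total sample size of 132 persons". The next sentence adds the allowance for loss: "With an estimated dropout rate of 20% a total of 159 patients is needed".

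Section 8.5 turns the inflated figure into a recruitment rule: "Inclusion is continued until 159 participants have been included". It does not provide for replacing dropouts beyond that number. The protocol gives no other dropout rate and no other method of inflation.

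Three further places bear on what dropout means for the analysis. Section 10.1 specifies an intention-to-treat linear mixed model over five measurement times. Section 10 says that patients with missing data stay in the analysis. Section 8.6 asks patients who stop treatment early to continue the assessments.

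**The concern.** Section 4.4 treats 132 as the number to protect and uses the 20% allowance to protect it. The three figures 132, 20% and 159 should then fit together, and they do not: a fifth taken off 159 leaves fewer than 132.

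Two things are at stake. First, a statement in the sample-size justification is false as it stands and can be checked from two adjacent sentences. Second, section 8.5 stops inclusion at the resulting number, so the slip carries from the justification into the conduct of the trial.

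**Working it through.** **Inputs from section 4.4:** effect size d = 0.43 (standardised, SD = 1), correlation ρ = 0.7, m = 5 measurements, power 0.80, α = 0.05, two arms, required total 132, dropout 20%, inflated total 159. **Assumed, because the protocol does not state them:** a two-sided test and 1:1 allocation.

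**Step 1. The base figure of 132.** With exchangeable correlation, the Liu-Liang equation for two equal arms is

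n per arm = 2 × [(z₀.₉₇₅ + z₀.₈₀) / d]² × [1 + (m − 1)ρ] / m.

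- The part before the variance factor is 84.90.
- The variance factor is (1 + 4 × 0.7) / 5 = 0.76.
- 84.90 × 0.76 = 64.52 per arm, a total of 129.05, or 130 with 65 per arm.

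This is close to 132. With m = 4 the factor is 0.775 and the total is exactly 132. A one-sided test with m = 5 gives 102, which does not fit. The stated 132 is therefore accepted.

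**Step 2. The stated 159.**

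- 132 × (1 + 0.20) = 158.4, rounded up to **159**. This reproduces the protocol's figure.
- 132 / (1 − 0.20) = **165**. This is the enrolment that leaves 132 after 20% loss, 6 more than stated.

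**Step 3. What 159 delivers.**

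- 159 × 0.80 = 127.2, so about **127 completers**, 5 fewer than 132.
- Largest dropout that still leaves 132: 1 − 132/159 = 0.170, or **17.0%**.
- Starting from the recomputed 130 does not rescue the figure: 130 / 0.80 = 162.5, or 163, still above 159.

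**Step 4. Effect on power.** On the same equation, power = Φ(d / √(2 × factor / n) − 1.96), where n is the number per arm.

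| Total | m = 5 (as stated) | m = 4 |
|---|---|---|
| 132 | 80.9% | 80.1% |
| 127 | 79.4% | 78.6% |

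The loss is about 1.5 points in either column. With m = 5, 127 falls 0.6 points below the 80% target. A small-sample version based on the non-central F distribution gives 80.3% and 78.8% for m = 5. The drop is the same, but those levels do not come from the equation that the protocol cites.

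**The case against.** The strongest reply is that the mixed model makes a count of completers too pessimistic. Sections 10 and 10.1 keep patients with incomplete data, and section 8.6 seeks assessments from those who stop treatment. Section 4.4 does not define dropout; if it includes stopping EMDR, some dropouts may have full data. On the formula above, the variance factor is 1 for a single measurement and 0.76 for five, so one usable measurement carries roughly 76% of a full patient's information. The shortfall of 132 − 127.2 = 4.8 patients would then be made up if about 7 of the roughly 32 dropouts (159 − 127) gave one post-baseline assessment, since 4.8 / 0.76 = 6.3.

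This stands as a limit on the consequence. A reader might infer from the arithmetic that the trial will have too few analysed patients or is materially underpowered. The protocol does not support that: 127 is a number of completers, and 79.4% assumes that every dropout contributes nothing.

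It does not remove the error. Section 4.4 offers no partial-data argument for 159; it presents 159 as what a 20% dropout requires, and on that basis the number is 165.

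A reader might also infer, in the other direction, that 159 is ample because a baseline-adjusted comparison at one time point would be more efficient. The protocol specifies no such test. Section 10.1 sets a Time and Group model with baseline as one of the five Time levels, so that argument cannot be used to justify 159.

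**Conclusion.** Wrong as written, and minor. The allowance multiplies by 1.2 where it should divide by 0.80, so 159 does not protect 132 at the stated dropout rate. The size is 6 patients at enrolment, 5 completers, and at worst about 1.5 points of power (80.9% to 79.4%).

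The dropout arithmetic needs no assumption beyond reading the 20% as a share of those enrolled. The power figures also assume a two-sided test, 1:1 allocation, exchangeable correlation and no information from dropouts. They apply to the quantity that the Liu-Liang calculation addresses. Nothing here calls for a change in design or analysis.

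**What to change.** One of two corrections is enough.

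1. **Keep 159.** Reword section 4.4 to say that 159 enrolled patients yield about 127 completers at 20% dropout, with about 79% power counting completers only, or 132 completers at 17% dropout. It may add that the mixed model also uses partial data, so the completer figure is a lower bound. Section 8.5 then stays as it is.
2. **Protect 132 at 20% dropout.** State 132 / 0.80 = 165 in section 4.4 and change the target in section 8.5 to 165, so that the two sections agree.

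The first option costs one sentence, no extra patients, and a slightly less favourable stated power. The second costs six more patients within the planned one-year inclusion period.
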